As per the BTF guideline, a stepwise approach will be preferred to regulate ICP management. Maintaining ICP < 25 mmHg and CPP > 60 mmHg are the target of the critical care treatment. Conventional therapies include head elevation (30°), ventilation, sedation, osmotic dehydration, external ventricular drainage and neuromuscular blockade. The short active propofol (5–100 μg/kg/min) and fentanyl (25–100 μg/h) are used for sedation. Mannitol (1 g/kg) is routine diuretic for osmotherapy. Equiosmolar hypertonic saline (23.4 %, 0.686 ml/kg in bolus) will be considered in patients with refractory intracranial hypertension or rebound phenomenon treated by mannitol. The short half-life of vecuronium (0.2 mg/kg/h) is selected for neuromuscular paralysis agent. Hyperthermia (32 °C–34 °C) will be added to the STBI patients when ICP is refractory even maximal medical treatment.

During critical care, repeated computed tomography (CT) scan will assess intracranial evolution if ICP > 20 mmHg. For craniotomy patients, salvage DC will be performed when there are deterioration of imaging findings (midline shift > 5 mm and/or cisternal compression) and malignant intracranial hypertension (ICP 25–30 mmHg > 1 h or ICP > 30 mmHg, regardless time). For DC patients, even there is no consensus on the optimal time of cranioplasty [35], and systematic review also questioned the definition of “early” which varies from 1 to 4 months [36, 37], it is rational to recommend bone flap replacement as early as 2 months after surgery once their performances achieving the clinical standard.

Scheduled CT scan will be performed at 1, 3, 7, 30 and 180 days after surgery. Additional CT scan will carry out depending on the condition of patient.

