### Follow-up and data collection

After randomization, patients will be assessed at 1 week and 1, 6 and 12 months. Patients who cannot be followed up at seven days will be assessed upon being discharged. For upfront exit patients, their surrogates should mark the previous data whether or not could be used in study. All patient information and imaging findings will be uploaded to a database using the case report form (CRF).

The initial data collection will be assessed at the emergency room by an attending physician. This collection will include baseline status, torso and/or extremities AIS, trauma severity (GCS, motor score and pupillary reaction), CT parameters (mass lesion type, volume of haematoma and midline-shift), time of injury-to-operation, cause of injury and initial laboratory features (arterial blood gas parameters, coagulation and platelet count).

The 1-week follow-up will include intra-operative brain swelling event, salvage craniectomy, laboratory features, early complications and ICP and CPP control. Intra-operative monitoring values will be recorded at the point of probe fixation, dura incision, dura suture and scalp closure. Post-operative ICP control will be recorded as daily ICP burden (number of hrs/d with ICP > 25 mmHg) and total ICP burden (number of days with ICP > 25 mmHg), as well as the same method recording daily and total CPP burden (CPP < 60 mmHg) [38].

At 1, 6 and 12 months follow-up, the independent blinded assessor will face-to-face evaluate intervention outcomes, quality of life, late complications and time of cranioplasty using standard questionnaire. The questionnaire includes the Extended Glasgow Outcome Score (GOSE), EQ-5D. If the discharged patients cannot attend scheduled follow-up, especially at time point of 6 or 12 months, the questionnaire will be sent to the documented permanent address. Only if these methods are invalid, the surrogate will be investigated to finish the questionnaire by telephone.

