### Outcomes

The Primary endpoint is a favorable outcome at 12 months after randomization as measured by GOSE (5–8). The core secondary endpoint is the quality of life indicated by EQ-5D. Further secondary endpoints include mortality and complications at corresponding time point, ICP and CPP control and incidence of salvage DC in craniotomy patients.

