### Statistical analysis

The analysis will be processed on the principle of intention. Patients who drop out or violate initial distribution will be considered as the worst outcome. Considering the probability of craniotomy patients treated by salvage DC, an as-treated analysis will also be implemented, as recommended in two-arm clinic trial [39]. Parametric data will be described by mean and standard deviation. Non-parametric data will be described by median and quartile. Categorical data will be presented using number and percentage.

The primary outcome of the study will be evaluated using the Pearson chi-square test with unadjusted risk ratio and 95 % confidence interval. Adjusted analysis of primary outcome will be assessed using logistic regression for pre-specified factors and any other covariates presenting significant difference between the two groups. The pre-specified subgroups include: age, GCS, pupillary response, mass lesion type and hypotension. Secondary outcome including assessment of quality of life, mortality at 6 and 12 months and incidence of complications will also be assessed using unadjusted analysis and adjusted regression. To investigate the risk factors of postoperative refractory hypertension (salvage DC), univariate and multivariate analysis will be used to identify potential variables of craniotomy patients.

Depending on the results of regression models, the receiver operating curves will be used to evaluate the discrimination. The Hosmer–Lemeshow test will process the goodness-of-fit of models [40]. A P value < 0.05 is considered statistically significant. All statistical analysis will be computed by SPSS software (version 19.0).

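### Scoring every drop-out as unfavourable on the 12-month GOSE dilutes a true difference and, if loss differs between arms, can create a false one

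*Protocol article*

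**What the plan says.** The rule stands in the protocol article under Statistical analysis, directly after the commitment to an intention-based analysis: "Patients who drop out or violate initial distribution will be considered as the worst outcome". No exception is made for what was last observed. This point concerns the drop-out half of that sentence only.

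The endpoint it acts on is under Outcomes: "The Primary endpoint is a favorable outcome at 12 months after randomization as measured by GOSE (5–8)". It is to be "evaluated using the Pearson chi-square test with unadjusted risk ratio and 95 % confidence interval".

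Follow-up and data collection shows what else is known about a lost patient: "At 1, 6 and 12 months follow-up, the independent blinded assessor will face-to-face evaluate intervention outcomes". The instrument is the same at each visit: "The questionnaire includes the Extended Glasgow Outcome Score (GOSE), EQ-5D". Patients who cannot attend are sent the questionnaire by post, and if that fails the surrogate is telephoned. For patients who leave early, "their surrogates should mark the previous data whether or not could be used in study".

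The as-treated analysis, the other analysis named, is there for salvage craniectomy and does not deal with missing outcomes. Sample size allows 10% for drop-out and gives no split by arm.

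**The concern.** On a yes/no endpoint, worst outcome means unfavourable. A patient rated favourable at 6 months and then truly lost, with the visit, post and telephone all having failed, is counted as a failure. The 1- and 6-month GOSE play no stated part.

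Such a rule is often called conservative, but in a two-arm comparison it is not reliably so. Each arm's observed rate is its true rate minus the favourable patients it lost, so the arm that loses more of them looks worse. More loss in the prophylactic arm pushes the result towards the trial's hypothesis; more loss in the therapeutic arm hides it. Even equal loss reduces the risk difference and the power. All of this falls on the primary result.

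**Working it through.** **Inputs from the protocol.** Favourable rates of 38% (prophylactic) and 54% (therapeutic), 168 per arm, two-sided 5%, 80% power and 10% drop-out (Sample size); uncorrected Pearson chi-square (Statistical analysis).

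**Assumptions not in the protocol.**
- The split of loss by arm: 10/10, 12/8 or 15/5, with the total held at 10%.
- A common true rate of 46% for the null case, midway between 38% and 54%.
- Who is lost: either (A) loss unrelated to survival, or (B) only survivors lost, with 35% mortality in both arms. The Background gives 30% to 50% mortality for severe injury.
- Within each scenario, lost patients have the same chance of a favourable outcome as those who stay (in B, as other survivors).

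**The plan's own figure.** The pooled normal formula for 38% versus 54% gives 152 per arm. Then 152 × 1.10 = 167.2, rounded up to 168; dividing by 0.90 instead gives 169. The arcsine formula gives 151, and 151/0.90 = 167.8, rounded up to 168. The stated 336 is reproduced. This sizing treats drop-outs as removed: 151 analysed per arm (168 × 0.90) has 80% power. The analysis rule instead keeps them as failures.

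**Formulas.** With true rate p and loss L in an arm, the observed rate is:
- A: p × (1 − L)
- B: p − L × p/0.65, where p/0.65 is the favourable share among survivors

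Rejection rates come from exact binomial enumeration of the chi-square test at 168 per arm.

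**No true difference (46% in both arms).** In B the favourable share among survivors is 0.46/0.65 = 71%.

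| Loss | Scenario | Observed rates | False difference | Rejection |
|---|---|---|---|---|
| 10% / 10% | A | 41.4% / 41.4% | 0 | 5.3% |
| 12% / 8% | A | 40.5% / 42.3% | 1.8 points | 6.6% |
| 12% / 8% | B | 37.5% / 40.3% | 2.8 points | 8.4% |
| 15% / 5% | A | 39.1% / 43.7% | 4.6 points | 14.2% |
| 15% / 5% | B | 35.4% / 42.5% | 7.1 points | 26.6% |

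The arm with more loss looks worse, so the sign depends on which arm that is. In A the false risk ratio (less loss over more) is simply the ratio of retention: 0.92/0.88 = 1.05 or 0.95/0.85 = 1.12.

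**True 54% versus 38%.**
- Equal 10% loss, A: 48.6% − 34.2% = 14.4 points, power about 77%. The risk ratio stays at 1.42, so the loss is in the difference and the power.
- Equal 10% loss, B: 45.7% − 32.2% = 13.5 points, power about 72%.
- 15% loss therapeutic, 5% prophylactic: 9.8 points (A, power about 45%) or 6.5 points (B, about 23%).
- The reverse split: inflated to 19.0 points (A) or 20.6 points (B).

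**The case against.** The rule is pre-specified, transparent and applied alike in both arms. Nothing in the protocol says that loss will be unequal. The three-step follow-up should keep true loss small, and the rule concerns patients who drop out, not those who miss one visit and are reached by post or telephone. If every lost patient truly had a poor outcome, there would be no bias. The large figures need a 3:1 imbalance; with survivors-only loss, 15% versus 5% means 23% of survivors lost in one arm (0.15/0.65) against 7.7% in the other (0.05/0.65). At equal 10% loss, the standard deviation of a chance gap between arms is √(2 × 0.1 × 0.9/168) = 3.3 points, so a 10-point gap is about three of them.

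Most of this stands, and it limits the size. It does not remove the defect: the rule is stated without exception, it dilutes the difference even with balanced loss, and nothing in the protocol supports the idea that all lost patients fared badly.

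A reader might infer that the design itself makes unequal loss likely, because patients without a bone flap are recommended a later replacement ("it is rational to recommend bone flap replacement as early as 2 months after surgery") and so have a reason to return that others lack. The protocol does not support this. Scheduled CT runs to day 180 and outcome visits to 12 months for all patients, and the flap may be off in either arm, through swelling at operation or salvage surgery. Unequal loss is possible here, not predicted.

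**Conclusion.** The point holds in conditional form. As written, a missing 12-month GOSE counts as unfavourable regardless of earlier GOSE. Under the planned rates, balanced 10% loss cuts the difference from 16 points to 14.4 or 13.5, and power to about 77% or 72%. Under no true difference, balanced loss does no harm. A mild 12/8 split gives a false difference of 1.8 to 2.8 points and a rejection rate of 6.6% to 8.4%. The 15/5 figures (4.6 to 7.1 points, 14% to 27%) mark an extreme and are not a forecast. All sizes rest on the assumed split of loss, the 46% common rate and, for the upper values, 35% mortality with only survivors lost. The documents do not say which arm would lose more, so neither does this point. The change is worth making because it concerns the primary result and is cheap.

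**What to change.** In the Statistical analysis section:

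- Use the observed 12-month GOSE wherever it is obtained, by visit, post or telephone, and enter known deaths as deaths.
- For values still missing, make multiple imputation within arm the primary handling. Use the baseline factors, and the 1- and 6-month GOSE where the surrogate permits use of earlier data.
- Keep worst-outcome scoring of all drop-outs as a stated sensitivity analysis.

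The cost is a change of wording and a few hours of programming; no new data are needed. The primary result would then rest on a missing-at-random assumption, which the retained worst-outcome analysis helps to probe. The gain is limited for patients whose earlier GOSE is absent or whose surrogate refuses its use.

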### Sample size

The sample size calculation is on the basis of the variance of outcomes. The favorable outcome of DC in previous studies ranged from 30 % to 61 % [9, 15, 41–43]. Some results may not be applicable because they included patients with diffusion injury and used DC as a secondary therapy. When primary DC treated patients for mass lesions, the favorable outcome of prophylactic DC in 781 patients was 38 % [44–54]. In our centre using therapeutic DC, the favorable outcome of therapeutic DC was 54 % [30]. After including a safety margin of 10 % to account for patients who drop out, we calculate that a sample size of 336 (each arm 168) will be sufficient to reach a significance level of 5 % (two-side) and a power of 80 %. The sample size will be re-assessed and adjusted during interim analysis.

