### Randomization

Computer-based central randomization will allocate treatment with minimizing following covariates: age (<40 or ≥ 40 years), GCS (8-6 or 5-3), pupillary response (both reactive or one reactive or no reactive), mass lesion type (subdural or intracerebral) and hypotension. A random element will be introduced to enhance the unpredictability of the minimization algorithm [55]. Physicians can use telephone or computer to register and randomize eligible patients. The patients will be assigned to either the therapeutic DC group or the prophylactic DC group and will receive a unique identity number for PRECIS records.

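### The primary chi-square ignores the five factors on which allocation is minimised, so it is conservative if they are prognostic; a pre-fixed adjusted analysis should be primary at no cost in patients

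*Protocol article*

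**What the plan says.** The Outcomes section defines a binary primary endpoint: "The Primary endpoint is a favorable outcome at 12 months after randomization as measured by GOSE" 5–8.

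The Randomization section says "Computer-based central randomization will allocate treatment with minimizing following covariates" and lists age, GCS, pupillary response, mass lesion type and hypotension. It adds: "A random element will be introduced to enhance the unpredictability of the minimization algorithm". The probability used for that element is not given.

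The Statistical analysis section fixes the primary test: "The primary outcome of the study will be evaluated using the Pearson chi-square test with unadjusted risk ratio", with a 95% confidence interval. It then plans a second analysis: "Adjusted analysis of primary outcome will be assessed using logistic regression for pre-specified factors and any other covariates presenting significant difference". The difference meant is one at baseline, comparing the arms. The next sentence reads: "The pre-specified subgroups include: age, GCS, pupillary response, mass lesion type and hypotension". These are the five minimisation factors, but they are called subgroups. The section never says expressly that they are also the adjustment set.

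The Sample size section compares two unadjusted proportions, 38% and 54%, at two-sided 5% and 80% power, with a 10% allowance for dropout. The result is 336 patients, 168 per arm.

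**The concern.** Minimisation holds the arms close together on the five factors, so little of the chance difference between arms can come from them. The Pearson chi-square and the unadjusted interval use a variance that still counts outcome variation due to those factors as noise. If the factors predict outcome, that variance is too large for this design, so P values are too large and intervals too wide. A test that conditions on the factors has close to the nominal error rate and more power.

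The planned regression does not settle this. It is not named as primary, its fixed covariates are not clearly listed, and further covariates enter if they happen to differ significantly at baseline. A model partly chosen from the data is a weak fallback if the two analyses disagree. At stake is precision: a real effect could be missed that data already collected for allocation would help to detect.

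**Working it through.** **1. The plan's own sample size.** Inputs from the Sample size section: 0.38 and 0.54, two-sided 5%, 80% power, 10% dropout. With pooled variance under the null and mean rate 0.46:

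n = [1.96·√(2·0.46·0.54) + 0.84·√(0.38·0.62 + 0.54·0.46)]² / 0.16² ≈ 151.1, so 152 per arm.

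Inflation gives 152 × 1.10 = 167.2, so 168 per arm (336), or 152/0.90 = 168.9, so 169 per arm (338). The stated 336 is reproduced. Power of the unadjusted comparison is 80.2% at 152 per arm and 84.0% at 168.

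**2. Formula, assuming exact balance on the factors.** Let R² be the share of outcome variance that the five factors explain. The documents give no value, so 10%, 20% and 30% are assumed. The true variance of the difference is (1 − R²) times the one that the chi-square uses. For a design with nominal 80% power (1.96 + 0.84 = 2.80):

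- chi-square type I error = 2[1 − Φ(1.96/√(1 − R²))]
- chi-square power = Φ(0.84/√(1 − R²))
- adjusted power = Φ(2.80/√(1 − R²) − 1.96)

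| R² | chi-square type I error | chi-square power | adjusted power |
|---|---|---|---|
| 10% | 3.9% | 81% | 84% |
| 20% | 2.8% | 83% | 88% |
| 30% | 1.9% | 84% | 92% |

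**3. Simulation at 336 patients.** Minimisation on the five factors with a biased-coin probability of 0.80; 4,000 runs per cell; no dropout; 38% in both arms under the null and 38% v 54% under the alternative. The adjusted model has arm plus main effects, with two indicators for pupils. Factor prevalences, effect sizes and the coin probability are assumptions.

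| Factor strength | R² | AUC | Type I error, chi-square / adjusted | Power, chi-square / adjusted | Gap (points) |
|---|---|---|---|---|---|
| none | 0 | 0.50 | 5.45% / 5.48% | 85.30% / 84.92% | −0.4 |
| weak | 0.035 | 0.61 | 4.32% / 4.75% | 84.15% / 84.45% | 0.3 |
| moderate | 0.126 | 0.71 | 4.15% / 5.60% | 85.95% / 88.32% | 2.4 |
| strong | 0.262 | 0.80 | 2.25% / 5.15% | 87.45% / 92.65% | 5.2 |

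The Monte Carlo standard error is about 0.35 points for type I error and 0.5 points for power. The adjusted error rates are all within two standard errors of 5%.

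As a control, arms of 168 randomised without regard to the factors gave a chi-square type I error of 5.15% (moderate) and 5.10% (strong). The conservatism therefore comes from combining minimisation with an unadjusted test.

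**The case against.** Four objections have weight.

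- **The planned power is not lost.** A reader might infer that the trial forfeits power it has paid for. The documents do not support that: 336 was sized for an unadjusted comparison, and the chi-square delivers 80.2% at 152 per arm and 84.0% at 168. The gain from adjustment was never part of the sample size. If 10% of each arm drop out and are counted as the worst outcome, as the Statistical analysis section provides, unadjusted power at 168 per arm is 76.6% (34.2% v 48.6%). That shortfall comes from the dropout rule and is a separate matter.
- **The error is in the safe direction.** A reader might fear a spurious claim of benefit. Neither the formula nor the simulation shows any excess of false positives from this mismatch.
- **The size is uncertain and may be small.** Age and GCS enter minimisation in two categories each, eligibility narrows their range, and the random element makes balance inexact. Counting 10% dropouts as failures, if unrelated to the factors, shrinks R² by about 17%: 10/20/30% become about 8/17/25%, and type I error about 4.1/3.2/2.4%.
- **An adjusted analysis is already planned.** It would be wrong to say that the plan ignores the factors. The five are the only pre-specified variables listed beside the regression, so they are probably meant as its core.

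All four limit the size of the point. None gives a reason to prefer the unadjusted test as primary, and the last leaves the baseline-significance rule in place.

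One might also object that a risk ratio from the primary analysis and an odds ratio from the regression conflict. At 54% v 38% they are 0.54/0.38 = 1.42 and (0.54/0.46)/(0.38/0.62) = 1.92. They are different measures, and the article does not say that the regression will be reported only as an odds ratio. This is a minor reporting matter.

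**Conclusion.** The design and the primary test do not match. If the five factors are prognostic, the primary P value and interval are conservative: type I error is about 4% at moderate and 2–3% at strong prognostic value. With weak or no prognostic value there is little or nothing to correct. The forgone power is about 0 to 6 points once simulation error is allowed for (largest simulated gap 5.2), and up to about 8 by formula at R² 30%.

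The direction is firm wherever the factors carry prognostic information. The size rests on assumed prognostic strength, factor prevalences and coin probability. The trial is valid and meets its stated power without the change, so this is an improvement worth making and not a threat to the result. The rule that admits covariates on baseline significance should go in any case.

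**What to change.** In the Statistical analysis section:

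1. Name as primary a logistic regression of GOSE 5–8 at 12 months on arm plus age, GCS, pupillary response, mass lesion type and hypotension, in the categories used for minimisation.
2. State that this covariate list is fixed, and delete the provision for adding covariates that differ significantly at baseline.
3. Report the standardised (marginal) risk ratio and risk difference with 95% confidence intervals, so that the adjusted and unadjusted results are on the same scale.
4. Keep the Pearson chi-square and unadjusted risk ratio as supportive analyses.

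Make the change before anyone who decides on the analysis has seen outcomes by arm.

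The cost is wording and some programming; check that the named software can produce intervals for standardised estimates. The sample size stays at 336. All five factors are needed for allocation, so they are known for every randomised patient. They use six parameters (two for pupils) against about 168 × (0.38 + 0.54) ≈ 155 expected favourable outcomes, or about 139 if 10% of patients drop out and count as unfavourable.

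### Part of the adjusted model is chosen by significant differences between the arms, which selects on chance imbalance; the covariates should be named in advance and limited to pre-randomisation variables

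*Protocol article*

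**What the plan says.** All of the following is in the protocol article.

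- **Primary test (Statistical analysis).** The primary outcome, favourable GOSE at 12 months, is "evaluated using the Pearson chi-square test with unadjusted risk ratio and 95 % confidence interval". No covariates enter it.
- **Adjusted analysis (same section).** The primary outcome is also analysed by logistic regression, with the pre-specified factors plus "any other covariates presenting significant difference between the two groups". The only threshold given is "A P value < 0.05 is considered statistically significant". Adjusted regression is planned for quality of life, mortality and complications too, with no separate covariate rule.
- **Factors named in advance.** The same section states: "The pre-specified subgroups include: age, GCS, pupillary response, mass lesion type and hypotension". The Randomization section lists the same five: "Computer-based central randomization will allocate treatment with minimizing following covariates". The article does not say outright that these are the pre-specified factors of the regression, but no other candidates are named.
- **Variables open to the screen (Follow-up and data collection).** The initial data include extracranial AIS, motor score and "CT parameters (mass lesion type, volume of haematoma and midline-shift), time of injury-to-operation, cause of injury and initial laboratory features". The 1-week data include laboratory features, early complications, ICP and CPP burden, and salvage craniectomy.

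**The concern.** Allocation is random, by minimisation with a random element. If a baseline variable outside the minimisation set differs at P < 0.05, that is the play of chance. Its P value measures the size of an accident. It does not measure the relation between the variable and GOSE, which is what makes adjustment worthwhile. A rule built on that P value can bring in a variable with no bearing on outcome and pass over a prognostic one that happens to be balanced.

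Two consequences follow. First, part of the adjusted model is settled only once the arms have been compared, so the adjusted estimate depends on a preliminary test. Second, the clause sets no time limit. Variables recorded after the bone-flap decision, such as ICP burden or early complications, may differ because of the treatment. Conditioning on them could remove part of the effect that the trial is meant to estimate.

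The adjusted analysis matters because the chi-square test ignores the minimisation factors. The regression is the planned analysis that can take account of how patients were allocated.

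**Working it through.** **1. Does the clause touch the design figures?** Inputs from the Sample size section: 38% versus 54% favourable, two-sided 5%, power 80%, 10% margin. With the pooled formula and no continuity correction:

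n = [1.960·√(2·0.46·0.54) + 0.842·√(0.54·0.46 + 0.38·0.62)]² / 0.16² ≈ 151.1, so 152 per arm.

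152 × 1.10 = 167.2, so 168 per arm and 336 in total. The stated size is reproduced. It rests on an unadjusted comparison of proportions, so the clause does not bear on it.

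**2. How many variables are open to the screen?** Named baseline items outside the five factors:

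- Seven are clear: extracranial AIS, haematoma volume, midline shift, cause of injury, blood gas, coagulation, platelet count.
- Two are doubtful. Motor score is a component of GCS, which is minimised. Injury-to-operation time is completed only after allocation, because the Interventions section starts the intervention once consent and randomisation are confirmed.
- Splitting the laboratory items raises the count. Fifteen is taken as the upper end, as an assumption.

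**3. Chance that at least one enters by luck.** With k independent tests at 5%, the probability is 1 − 0.95^k.

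| k | Probability |
|---|---|
| 7 | 30% |
| 9 (with the two doubtful items) | 37% |
| 10 | 40% |
| 12 | 46% |
| 15 | 54% |

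Positive correlation between the variables would lower these figures.

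**4. What does the rule do to the analysis?** A simulation of 2,000 trials per scenario was run at N = 336, with simple equal allocation. There were ten extra baseline covariates, three of them prognostic with a log odds ratio of 0.7 per SD. All these settings are assumptions. The treatment log odds ratio was 0 or 0.65, the latter from ln[(0.54/0.46)/(0.38/0.62)]. The five core factors were not modelled.

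| Logistic model | Rejection, no effect | Rejection, effect present |
|---|---|---|
| Unadjusted | 5.2% | 64% |
| Covariates selected by the rule | 4.9% | 63% |
| Three prognostic covariates fixed in advance | 4.7% | 73% |

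At least one covariate was selected in 40% of trials under no effect and in 38% with an effect. About 71% of those selected were not prognostic, against 7/10 = 70% of the candidates, so the screen picked without regard to prognosis. The Monte Carlo standard error of a 5% rejection rate is √(0.05·0.95/2000) ≈ 0.5 points, so the three rates under no effect cannot be told apart. The power values compare the three models and are not estimates of this trial's power.

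**5. Are post-randomisation variables excluded?** The clause refers to any other covariates without a time restriction. The Randomization section uses the word only for pre-randomisation characteristics, and the Outcomes section classes complications and ICP/CPP control as secondary endpoints. Both suggest that baseline variables were meant, but neither says so.

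**The case against.** The strongest reply is that this is a supporting analysis. The main test, its significance level and the sample size do not depend on the clause. That stands, and it limits the weight of the point.

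Four stronger readings are tempting, and the documents do not support them:

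- **The adjusted model is wholly unknown until the data are seen.** It is not. The pre-specified factors come first and apparently are the five minimisation factors. Only the added part depends on the data.
- **Post-operative variables will be adjusted for.** The article does not say this, and its usage elsewhere points the other way. It only fails to rule them out, and a restriction could sit in a fuller document that is not shown.
- **The screen inflates type I error.** The simulation shows no inflation (4.9%), and power was close to that of the unadjusted model. The harm is a missed gain, and its size depends on how strongly the assumed covariates predict outcome.
- **The chance of an altered model is a firm 37%.** That figure counts motor score and injury-to-operation time and assumes independence. It is also the chance that a variable enters, not the chance of a wrong conclusion. Only a range can be defended.

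It is also fair to say that no section of the article states that midline shift or haematoma volume predicts GOSE. Naming them is therefore for the trial team to decide.

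The objection does not rescue the rule. The article states the selection criterion, so this is not a detail left to an analysis plan, and the criterion is unrelated to the purpose of adjustment.

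**Conclusion.** The point holds in limited form. The clause selects the added covariates on chance imbalance rather than prognosis. This affects the adjusted analysis of the primary outcome and, if the same rule is used there, the adjusted secondary analyses.

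With 7 to 15 independent extra baseline variables, both assumed, luck alone would change the model in roughly 30% to 54% of trials. Under the simulated settings the rule gained nothing over no adjustment (63% against 64%) and gave up about 10 points of power against a fixed prognostic set (73%). The lack of an explicit bar on post-randomisation variables is an ambiguity to close, not a demonstrated bias. The change is worth making because the rule is poor and the remedy is almost free.

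**What to change.** Delete the clause on covariates that differ significantly. In its place, state that:

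1. The adjusted logistic model contains treatment arm and the five minimisation factors: age, GCS, pupillary response, mass lesion type and hypotension.
2. Any further covariates are named now, from baseline data already collected, and chosen for expected prognostic value. Midline shift and haematoma volume are examples.
3. Only variables measured before randomisation are eligible, and baseline significance tests are not used to select covariates.
4. The same list applies to the adjusted secondary analyses, or a different one is given.

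The cost is a sentence or two of analysis wording. Data collection, the primary chi-square test and the total of 336 patients do not change.
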